Despite modest progress, significant gaps persist in Pakistan’s infant and young child feeding (IYCF) indicators. The recent National Nutritional Survey reported improvements in EIBF from 40% (2011) [10] to 45% (2018) [3]; yet, nearly 40% of neonates continue to receive prelacteal feeds [3], undermining the benefits of colostrum feeding. Further, a nonlinear trend was found in EBF, decreasing from 50% (2001) [3] to 37.7% (2011) [10] before rising to 48% (2018) [3], reflecting inconsistent policies and nonsustainable interventions. The decline in EBF was particularly evident at 3 months of infant age, dropping from 84% to 70% [11], reportedly due to inadequate maternal knowledge about EBF and its associated benefits [12]. The continued breastfeeding practice at 1 year also declined from 77.3% (2011) [10] to 68.4% (2018) [3], with only 40.1% of children aged 0 to 23 months receiving age-appropriate breastfeeding [3]. This means that while initial breastfeeding practices may be improving, their maintenance and adherence remain inadequate and challenging. Further, the complementary feeding (CF) indicators were even more concerning. Only 36% of children aged 6‐8 months receive timely CF; minimum dietary diversity (MDD) is achieved by 14%, minimum meal frequency (MMF) by 18%, and a mere 3.6% of children meet the minimum acceptable diet (MAD) criteria [3], a composite indicator reflecting both meal frequency and diversity. These significant deficiencies impair infant physical growth, immunity, and cognitive development.

This alarming situation has not improved much, as a recent study conducted in rural Sindh Province reported that <10% of infants were EBF, with a significant proportion identified as wasted (14.7%), stunted (36.7%), and underweight (38.5%) at birth [13]. The study also found a significant association of early initiation of CF or breast milk alternatives before 4 months and increased odds of wasting by 6 months of age (adjusted odds ratio 4.14, 95% CI 1.95-8.77; *P*<.001) [13]. This further reflects persistent gaps in early child nutrition, which are the result of a complex interplay of inadequate maternal knowledge, sociocultural norms and myths, and insufficient nutritional counseling at health system touchpoints [14-16].

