#### Primary Outcomes

The primary end points of the study are (1) EBF at 6 months of infant age and (2) introduction of AACF [49,50] at 6 months of infant age.

In addition, EBF will also be assessed at the 6th, 10th, and 14th weeks, while CF practices will also be assessed at 9 months of infant age. The repeated assessments at additional time points will be used for longitudinal analyses to evaluate trends and sustainability of feeding practices over time. Operational definitions of the primary outcome measures are provided in Table 3.

**Table 3. T3:** Operational definitions of primary and secondary outcome measures.

Outcome	Operational definitions
Primary outcomes [49,50]	
Exclusive breastfeeding	Proportion of infants who are fed exclusively with breast milk up to 6 months of age
Introduction of age-appropriate complementary feeding	Proportion of infants who are introduced to solid, semisolid, or soft foods at 6 mos of age
Secondary outcomes	
Infant and young child feeding practices [49,50]	
Early initiation of breastfeeding	Proportion of children put to the breast within 1 hour of birth
Minimum dietary diversity	Proportion of children 6‐12 months of age who receive food from 4 or more food groups
Minimum meal frequency	Average number of daily meals for children 6‐12 months of age, who receive solid, semisolid, or soft foods
Minimum acceptable diet	Composite variable based on meal frequency and dietary diversity
Mean duration of breastfeeding	Average duration an infant is breastfeeding for 12 months
Continued breastfeeding at 1 y	Proportion of children 12 months of age who are still on breast milk
Child health	
ARI^a^	Short, rapid breathing that is chest-related and/or difficult breathing that is chest-related. Percentage of children up to 1 year of age with symptoms of ARI at any time in the last 2 weeks preceding the follow-up
Acute diarrhea	Passage of 3 or more loose or liquid stools per day (or more frequent passage than is normal for the individual). Percentage of children up to 1 year of age with symptoms of diarrhea at any time in the last 2 weeks preceding follow-up
Visit to the emergency room	Infant brought to the emergency room for management of any acute illness in past 2 weeks.
Hospitalization	Infant admitted to the hospital for diagnosis or management of any acute illness in past 2 weeks.

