### Statistical Analysis

#### Data Analysis Plan

Baseline characteristics will be summarized by randomized group using frequencies and percentages for categorical variables (eg, education, socioeconomic status, area of residence, and employment status) and mean (SD) or median (IQR) for continuous variables (eg, maternal age and parity), as appropriate. Normality of continuous variables will be assessed using the Shapiro-Wilk test. Baseline comparability will be evaluated using chi-square or Fisher exact tests for categorical variables and independent-samples *t* tests or Mann-Whitney *U* tests for continuous variables.

All primary and secondary analyses will follow the intention-to-treat principle, including all participants as randomized. Primary outcomes (EBF and AACF at 6 mo of infant age) are binary and will be analyzed using regression models appropriate for dichotomous outcomes. The results will be expressed as adjusted risk ratios or odds ratios with 95% CIs. Treatment effects will be reported with corresponding 95% CIs and 2-sided *P* values. Repeated measures of EBF (at the 6th, 10th, and 14th weeks) and CF practices will be analyzed using mixed-effects regression models with random intercepts to account for within-participant correlation and fixed effects for treatment group, time, and group-by-time interaction.

Secondary outcomes that are binary, including EIBF, continued breastfeeding at 1 year, MDD, MMF, and MAD, will be analyzed using similar logistic regression approaches. Continuous secondary outcomes, including mean duration of breastfeeding and child anthropometric *z* scores (height-for-age, weight-for-height, and weight-for-age), will be analyzed using linear regression or linear mixed-effects models, with results reported as mean differences and 95% CIs.

Breastfeeding self-efficacy and mHealth usability will be measured using validated multi-item Likert-scale instruments. Composite scale scores will be generated by summing or averaging item responses and analyzed as continuous outcomes using linear or mixed-effects linear regression models, as appropriate. Distributional assumptions will be assessed, and robust standard errors or nonparametric methods will be applied in sensitivity analyses if substantial departures from normality are observed.

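### Table 3 defines minimum meal frequency as a mean among infants on solids, but the analysis plan treats it as a yes/no outcome in all randomised participants; minimum acceptable diet inherits the missing cut-off.

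*Protocol article*

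**What the plan says.** All statements are in the protocol article.

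- **Table 3, MMF row:** "Average number of daily meals for children" 6 to 12 months of age, "who receive solid, semisolid, or soft foods".
- **Table 3, MAD row:** "Composite variable based on meal frequency and dietary diversity". No cut-off or combining rule is given.
- **Table 3, minimum dietary diversity (MDD) row:** a proportion of children 6 to 12 "months of age who receive food from 4 or more food groups". This row does have a cut-off.
- **Data Analysis Plan, binary outcomes:** "Secondary outcomes that are binary, including EIBF, continued breastfeeding at 1 year, MDD, MMF, and MAD, will be analyzed using similar logistic regression approaches".
- **Data Analysis Plan, continuous outcomes:** "Continuous secondary outcomes, including mean duration of breastfeeding and child anthropometric" z scores. MMF is not named here.
- **Data Analysis Plan, population:** "All primary and secondary analyses will follow the intention-to-treat principle, including all participants as randomized".
- **Introduction:** MMF is given as a share of children achieving it, "minimum meal frequency (MMF) by 18" percent.
- **Outcome Assessment and Schedule:** the outcome indicators are said to derive from the WHO infant and young child feeding (IYCF) indicators. Table 2 schedules MMF, MDD and MAD at 6, 9 and 12 months.

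**The concern.** The operational definition and the planned model do not fit each other. Logistic regression needs a yes/no value for each infant, and a mean meal count supplies none. An analyst who follows Table 3 would report mean meals. One who follows the Data Analysis Plan would report the proportion above some threshold. These are different outcomes, and a threshold chosen after the data are seen would not be credibly prespecified.

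The second issue is who is counted. The MMF row describes children already receiving solid, semisolid or soft foods. Introduction of such foods at 6 months is one of the two primary outcomes. If the row is applied as written, the app can change who enters the MMF comparison, and the two groups compared are no longer the randomised ones. That conflicts with the statement that secondary analyses include everyone as randomised.

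**Working it through.** No sample size or power figure is in dispute, so there is no figure of the plan to reproduce. The check has two parts.

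**1. Definition against analysis**

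| Outcome | Table 3 | Cut-off in Table 3 | Data Analysis Plan |
|---|---|---|---|
| MDD | Proportion | Yes, 4 or more food groups | Binary, logistic |
| MMF | Mean count among infants on solids | None | Binary, logistic |
| MAD | Composite of meal frequency and diversity | None for meal frequency; no combining rule | Binary, logistic |

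MDD is consistent across the two places. MMF is not. MAD needs a yes/no meal-frequency component, and Table 3 supplies none.

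**2. Effect of the literal MMF denominator at 6 months**

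Inputs from Sample Size: 150 per arm; introduction of age-appropriate complementary feeding 50% in the control arm; planned absolute difference 20 points, hence 50% + 20% = 70% in the intervention arm.

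Assumption: the share of infants on solids at the 6-month visit equals these rates. Infants started on solids earlier would also be on solids, so the true shares could differ.

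Infants kept by the MMF row:
- control: 0.50 × 150 = 75
- intervention: 0.70 × 150 = 105
- left out: 75 + 45 = 120 of 300 (40%), that is 50% of control and 30% of intervention infants

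With 20% missing in each arm (120 left), the counts are 0.50 × 120 = 60 and 0.70 × 120 = 84, the same proportions.

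Let p be the share of infants on solids who meet the minimum, assumed equal in both arms. The article does not give p.
- infants on solids only: p against p, difference 0 for every p
- all infants, with those not on solids counted as not meeting it: 0.5p against 0.7p, difference 0.2p

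| p | On solids only | All infants | Difference, all infants |
|---|---|---|---|
| 20% | 20% vs 20% | 10% vs 14% | 4 points |
| 60% | 60% vs 60% | 30% vs 42% | 12 points |

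The equal-p assumption forces the zero in the second column, so I relaxed it. Let the additional 20% of intervention infants who start solids meet the minimum at rate q. The restricted intervention proportion is then (0.5p + 0.2q)/0.7, and the all-infant proportion is 0.5p + 0.2q. Take p = 36% as an illustration (the Introduction's 18% divided by 50%):
- q = 36%: restricted 36% vs 36%; all infants 18% vs 25.2%
- q = 18%: restricted 36% vs 0.216/0.7 = 30.9%; all infants 18% vs 21.6%
- q = 0: restricted 36% vs 0.18/0.7 = 25.7%; all infants 18% vs 18%

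So the restricted comparison can hide a gain among all infants (first case), reverse its sign (second), or show a deficit where there is no difference (third).

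With general shares on solids s_c and s_t and equal p, the all-infant difference is p(s_t − s_c). It shrinks as the arms converge, so a smaller imbalance is expected at 9 and 12 months.

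**The case against.** The best defence is that Table 3 contains one loosely condensed cell. The article says its indicators derive from the WHO IYCF indicators, the Data Analysis Plan classes MMF and MAD as binary, and the Introduction treats both as achieved or not. An article may leave exact thresholds to its sources. This stands as far as it goes: the cited indicators can supply a threshold, and the absence of a number would not by itself be a finding. It does not remove the contradiction, because Table 3 goes beyond omitting a threshold and states a different quantity.

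On the denominator, the defence is that in the neighbouring MDD row the similar clause gives the condition for being counted as a success. The MMF clause might likewise describe which feeds are counted, and the intention-to-treat statement favours that reading. This is a fair alternative. As written, however, the clause attaches to the children, and an average has no success condition for it to describe. The wording needs settling either way.

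A reader might also infer that MMF and MAD cannot be computed at all, or that MAD too is limited to infants on solids. The article supports neither. Infant-level meal counts are needed even for the mean in Table 3, so a yes/no value can be derived once the threshold is named. No restriction is written for MAD, and one could reach it only by inference through its meal-frequency component.

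**Conclusion.** The point holds as a contradiction between a stated definition and a stated analysis. As worded in Table 3, MMF cannot be the response in the planned logistic model, and MAD inherits the missing meal-frequency cut-off.

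The denominator problem is conditional on reading the MMF row literally. On that reading, and if the planning rates describe who is on solids at 6 months, about 75 against 105 of 150 per arm would be compared. The values of p and q are assumptions, and the illustration uses the earliest visit, where the imbalance should be greatest.

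Only secondary outcomes are affected. The co-primary analyses and the sample size are untouched. A reader might conclude that the main time point for these outcomes must move to 12 months. Nothing in the article requires that, because a fixed denominator works at each scheduled visit.

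**What to change.** Reword Table 3:

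- **MMF:** the proportion of all infants assessed at the visit who meet the minimum in the cited IYCF indicators. Infants not on solids count as not meeting it.
- **MAD:** the proportion of all infants assessed at the visit who meet both MDD and MMF at that visit.
- **Mean number of daily meals:** keep as a separate descriptive line.

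The Data Analysis Plan then stands as written, and missing visits fall under its existing missing-data rules. The cost is wording only, since the mean in Table 3 already requires a meal count for each infant.

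The change is best made before any 6-month data exist. Recruitment began on February 2, 2026. Even a birth on that day gives a 6-month date of August 2, or July 19 with the 2-week window, which is later than the latest recruitment date in the article (May 18, 2026).

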#### Secondary Outcomes

IYCFP-related secondary outcomes include EIBF, continued breastfeeding at 1 year, mean duration of breastfeeding, MDD, MMF, and MAD [49,50]. Child health–related secondary outcomes include acute respiratory infection, acute diarrhea, visits to the emergency room, hospitalization, stunting (height-for-age) [51], wasting (weight-for-height) [51], overweight (weight-for-height) [51], underweight (weight-for-age) [51], breastfeeding self-efficacy [52], and mHealth usability [53]. Operational definitions of the secondary outcome measures are provided in Table 3.

### Follow-Up

Outcome assessments are aligned with the national Expanded Programme on Immunization schedule to maximize participant adherence. These will be collected at birth; at the 6th, 10th, and 14th weeks; and at the 6th, 9th, and 12th months of infant age by the RA. At each follow-up visit, participants in both study arms will receive F2F counseling. Follow-up windows of ±2 weeks will be permitted to accommodate participant availability and logistical constraints. Phone call reminders will be given prior to their appointments, with the option to reschedule, where needed. When in-person visits would not be feasible, counseling and outcome data will be collected through telephone follow-up or during subsequent health facility visits to minimize loss to follow-up.

### Retention Strategy

The RA will remain engaged with all study participants fortnightly to maintain contact, confirm continued participation, and address any study-related or technical concerns. Participants in the intervention arm will be inquired regarding application functionality and, if necessary, provided assistance with troubleshooting or reinstallation of the app to ensure uninterrupted access. For participants in the control arm, the RA will maintain equivalent contact to minimize differential attention across study arms. Follow-up windows will remain flexible to accommodate participant availability, and alternative contact modalities will be used where needed. Attrition will be continuously monitored, and reasons for withdrawal will be documented. If attrition exceeds anticipated levels, this will be addressed analytically through intention-to-treat analyses, supported by sensitivity analyses using appropriate methods for missing data.

### Data Collection

Demographic information, including maternal age, education, employment status, maternity leave entitlements, income, ethnicity, area of residence, and obstetric history, will be collected electronically at the time of enrollment through a pretested structured questionnaire in Urdu. These factors will be examined in the analysis as potential confounders to assess their influence on IYCFP adherence and intervention outcomes. Study outcomes and anthropometric measurements will be recorded at each follow-up visit by the RA using standardized structured questionnaires. Participant knowledge, attitude, and breastfeeding self-efficacy will be collected at recruitment, the 14th week, and 12 months of infant age. The study schedule is reported according to the SPIRIT (Standard Protocol Items: Recommendations for Interventional Trials) 2013 statement.

### Data Management Plan

All study data will be collected electronically with predefined range and logic checks within the database to detect out-of-range values, inconsistencies, and missing data at the point of entry and during routine data cleaning. Version control procedures will be applied to all study datasets. Any modifications will be documented with version numbers, timestamps, and descriptions of changes. An audit trail will be maintained to automatically record all data creation, modification, and access events, including user identity and the date of change.

### Data Monitoring

All study data will be monitored in real time through a centralized digital dashboard. The Research Scholar will do day-to-day data monitoring, ensure protocol adherence at the study sites, and track participant adherence and withdrawals. The Principal Investigator will conduct fortnightly supervisory meetings, review study progress, and arrange periodic audits to ensure data quality and protocol compliance. RAs will receive refresher training periodically to address any identified quality issues.

### Adverse Events Monitoring, Reporting, and Management

Although the intervention is behavioral and noninvasive, anticipated harms include digital fatigue, psychological stress related to health messaging, technical issues such as app malfunction, and potential concerns related to data privacy. All potential adverse events will be actively monitored throughout the study period. Participants will be encouraged to report any discomfort, distress, or technical difficulties to the RA. All reported adverse events will be documented, reviewed, and categorized by type and severity. Serious or unexpected adverse events will be referred for consultation. Appropriate technical or supportive actions will be taken as needed, including temporary suspension of app notifications or technical troubleshooting.

### Data Security and Confidentiality

Participant data will be stored in a centralized, encrypted database hosted on secure servers, with role-based access controls to ensure that only authorized study personnel (the Principal Investigator and Research Scholar) can access identifiable information. Data transmission between the mobile app, backend servers, and web portal is protected using industry-standard encryption protocols (HTTPS). Personally identifiable information is stored separately from usage and engagement data to enhance privacy protection. The platform complies with established data protection and confidentiality principles, including secure authentication, password protection, and audit logging.

### Study Reporting Guidelines

This RCT protocol is reported according to the SPIRIT guidelines.

### Statistical Analysis

#### Data Analysis Plan

Baseline characteristics will be summarized by randomized group using frequencies and percentages for categorical variables (eg, education, socioeconomic status, area of residence, and employment status) and mean (SD) or median (IQR) for continuous variables (eg, maternal age and parity), as appropriate. Normality of continuous variables will be assessed using the Shapiro-Wilk test. Baseline comparability will be evaluated using chi-square or Fisher exact tests for categorical variables and independent-samples *t* tests or Mann-Whitney *U* tests for continuous variables.

All primary and secondary analyses will follow the intention-to-treat principle, including all participants as randomized. Primary outcomes (EBF and AACF at 6 mo of infant age) are binary and will be analyzed using regression models appropriate for dichotomous outcomes. The results will be expressed as adjusted risk ratios or odds ratios with 95% CIs. Treatment effects will be reported with corresponding 95% CIs and 2-sided *P* values. Repeated measures of EBF (at the 6th, 10th, and 14th weeks) and CF practices will be analyzed using mixed-effects regression models with random intercepts to account for within-participant correlation and fixed effects for treatment group, time, and group-by-time interaction.

Secondary outcomes that are binary, including EIBF, continued breastfeeding at 1 year, MDD, MMF, and MAD, will be analyzed using similar logistic regression approaches. Continuous secondary outcomes, including mean duration of breastfeeding and child anthropometric *z* scores (height-for-age, weight-for-height, and weight-for-age), will be analyzed using linear regression or linear mixed-effects models, with results reported as mean differences and 95% CIs.

Breastfeeding self-efficacy and mHealth usability will be measured using validated multi-item Likert-scale instruments. Composite scale scores will be generated by summing or averaging item responses and analyzed as continuous outcomes using linear or mixed-effects linear regression models, as appropriate. Distributional assumptions will be assessed, and robust standard errors or nonparametric methods will be applied in sensitivity analyses if substantial departures from normality are observed.

The extent and patterns of missing data will be examined. If more than 10% of outcome data are missing, multiple imputation using chained equations will be performed under a missing-at-random assumption. Imputed results will be compared with complete-case analyses in sensitivity analyses. Prespecified subgroup analyses will assess effect modification by maternal education, employment status, and parity through inclusion of interaction terms. All analyses will be conducted using Stata software (StataCorp), with statistical significance set at .05.

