**Methods:**

This is a prospective, parallel-arm randomized controlled trial planned at a secondary care hospital in Karachi, Pakistan. The study will enroll 300 booked singleton pregnant women in the third trimester, who plan to stay in their respective areas for at least 1 year postdelivery, are registered for child immunization at the associated Family Health Center, own smartphones with internet access, are able to read Urdu, and provide consent. Participants in the intervention arm will receive the *Pehli Ghiza* mHealth app along with routine standard-of-care F2F counseling. The app will deliver context-specific educational content on breastfeeding and IYCFPs through short videos and messages sent 3 times per week, tailored to the stage of pregnancy and infant age. Participants in the control arm will receive only routine F2F counseling. The standard of care will be delivered at each follow-up visit, which is scheduled at birth, at 6, 10, and 14 weeks, and at 6, 9, and 12 months of the infant’s age. Data will be collected at enrollment and at each follow-up visit using structured questionnaires. Primary outcomes are EBF and the introduction of age-appropriate complementary feeding. Secondary outcomes include early initiation of breastfeeding, continued breastfeeding at 1 year, minimum dietary diversity, meal frequency, minimum acceptable diet, and child health outcomes. Analysis will follow the intention-to-treat principle to detect a 20% absolute improvement in primary outcomes between the intervention and control groups over time and to evaluate between-group differences in feeding practices. Compliance will be determined by the proportion of participants who complete the 6-month coaching program. Usability will be assessed based on features related to design, interface, content, coaching, perception, and personal benefit.

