### Sample Size

The sample size was calculated to detect a 20% absolute difference in the primary outcomes between the intervention and control arms. The calculation assumed a baseline prevalence of EBF of 48% [3] and AACF of 50% [39] in the control group. Using a 2-sided significance level of 5%, statistical power of 80%, a 1:1 allocation ratio, and an anticipated 20% loss to follow-up in each study arm, a total sample of 300 pregnant women (150 per arm) was determined to be sufficient to detect the expected intervention effect. Loss to follow-up included participant withdrawal and/or discontinuation of app use in the intervention arm. Sample size estimation was performed using *OpenEpi* software (version 3.0).

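### The trial is sized on a 20-point absolute difference, but the primary effect measure is left open between risk ratio and odds ratio and no absolute difference is named

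*Protocol article*

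**What the plan says.** The target is absolute in two places. Sample Size states: "The sample size was calculated to detect a 20% absolute difference in the primary outcomes between the intervention and control arms". The control rates are also given there: "The calculation assumed a baseline prevalence of EBF of 48% [3] and AACF of 50% [39] in the control group". The abstract's Methods paragraph repeats the aim: "Analysis will follow the intention-to-treat principle to detect a 20% absolute improvement in primary outcomes between the intervention and control groups over time".

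The Data Analysis Plan assigns the two binary primaries at 6 months to an unnamed regression for binary data and continues: "The results will be expressed as adjusted risk ratios or odds ratios with 95% CIs". The next sentence promises confidence intervals and two-sided P values for treatment effects without naming a scale. The binary secondary outcomes get logistic approaches described as similar, which leans towards the odds ratio without fixing it. A difference scale is named only for the continuous secondary outcomes, as mean differences.

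On self-efficacy, Data Collection states: "Participant knowledge, attitude, and breastfeeding self-efficacy will be collected at recruitment, the 14th week, and 12 months of infant age". The Data Analysis Plan analyses the scale score by linear or mixed-effects linear regression and does not say how the recruitment score enters.

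**The concern.** The protocol does address the primary effect measure, and does so with an unresolved alternative. This is therefore more than a detail left to an analysis plan that is not shown. With outcomes as common as 48% to 70%, an odds ratio is far from a risk ratio and is easily read as one. An adjusted odds ratio has a further weakness: its value moves with the covariates in the model even when nothing is confounded.

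Two things are at stake. A reader given only a ratio cannot see directly how the effect compares with the 20 points that justified the sample size. And if the scale is settled after the data are seen, the larger-looking number could become the headline. Separately, a baseline measure of a secondary outcome is collected with no stated use in its analysis.

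**Working it through.** **Inputs.** From Sample Size: control rates p0 of 48% (EBF) and 50% (AACF), a 20-point difference, hence p1 of 68% and 70%; two-sided 5%, 80% power, 1:1 allocation, 20% loss, 150 per arm. Evaluable per arm: 150 × 0.8 = 120.

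**Step 1: the stated size.** n per arm = [1.96√(2p̄q̄) + 0.842√(p0q0 + p1q1)]² / (p1 − p0)². For EBF p̄ = 0.58, so n = (1.368 + 0.575)² / 0.04, which rounds up to 95, or 105 with continuity correction. Dividing by 0.8 gives 119 or 132 per arm, 238 or 264 in total. For AACF the totals are 234 or 258. The stated 300 is not reproduced, but it exceeds all of these, so calling it sufficient is true. That gap is a separate matter and does not bear on the effect measure.

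**Step 2: the same planned effect on each scale.** RR = p1/p0; OR = [p1/(1 − p1)] / [p0/(1 − p0)].

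| Outcome | Difference | RR | OR |
|---|---|---|---|
| EBF, 48% to 68% | 20 points | 0.68/0.48 = 1.42 | (0.68/0.32)/(0.48/0.52) = 2.30 |
| AACF, 50% to 70% | 20 points | 0.70/0.50 = 1.40 | (0.70/0.30)/(0.50/0.50) = 2.33 |

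**Step 3: what a fixed ratio means at another control rate.** With RR held, the difference is p0(RR − 1). With OR held, p1 = o/(1 + o), where o = OR × p0/(1 − p0). Using the EBF ratios (RR 1.417, OR 2.302):

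| Control rate | Difference if RR 1.417 | Difference if OR 2.302 |
|---|---|---|
| 10% | 4.2 points | 10.4 points |
| 30% | 12.5 | 19.7 |
| 48% (planned) | 20.0 | 20.0 |
| 60% | 25.0 | 17.5 |
| 70% | 29.2 | 14.3 |

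Rates other than 48% are illustrative assumptions. The Introduction shows why the control rate is uncertain: it cites 48% EBF nationally and under 10% in a rural Sindh study. For AACF it cites 36% timely complementary feeding at 6 to 8 months, an age band rather than the 6-month endpoint itself. At 36%, RR 1.40 means 0.36 × 0.40 = 14.4 points, while OR 2.33 means 1.3125/2.3125 − 0.36 = 20.8 points.

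**Step 4: does the scale cost power?** At 120 per arm, unadjusted:

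| Outcome | Test of proportions | Log RR | Log OR |
|---|---|---|---|
| EBF | 88.6% | 86.5% | 87.6% |
| AACF | 89.0% | 86.9% | 88.0% |

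The scale hardly matters for power.

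**Step 5: precision of a risk difference.** Half-width = 1.96√[(p0q0 + p1q1)/120]. EBF: 1.96√(0.4672/120) = 12.2 points. AACF: 1.96√(0.46/120) = 12.1 points. No change in sample size is needed.

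**Step 6: baseline self-efficacy.** With the baseline score as covariate, residual variance is multiplied by 1 − r², relative to an analysis that ignores baseline. The documents give no r. At assumed values of 0.3, 0.5 and 0.6 the factor is 0.91, 0.75 and 0.64, a reduction of 9%, 25% and 36%. At r = 0.5 this is worth 1/0.75 = 1.33 times as many women for that outcome.

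**The case against.** The case against is substantial, and most of it limits the point without removing it.

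- A reader might infer that the absolute effect will never be estimated. The text does not support that. It does not exclude a risk difference, which can be had from the arm proportions or from the same regression. The gap is that none is named.
- A reader might infer that 20 points defines success. It does not. Sample Size uses it as the planning effect, and the abstract speaks of detecting it; neither makes it a threshold.
- Sizing on a difference and reporting a ratio is no error in itself. The null hypothesis is the same and power is nearly equal (step 4), so the open choice affects presentation and interpretation far more than the test.
- A reader might infer that covariates will be picked by baseline significance tests. Data Collection says of the demographic factors: "These factors will be examined in the analysis as potential confounders to assess their influence on IYCFP adherence and intervention outcomes". The Data Analysis Plan runs baseline tests to describe comparability. Neither place says that test results decide adjustment, and the covariate list may properly stand in an analysis plan that is not shown.
- A mixed model over the three self-efficacy waves could already use the recruitment score. That stands: the article is silent here, and the variance gain applies only against an analysis that ignores baseline. Naming the covariate is an improvement, not the correction of a stated mistake.

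What remains is that the protocol names two alternative primary measures, chooses neither, and names none on the scale of its own target.

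**Conclusion.** The point holds in a limited form. The protocol is framed and sized on 20 absolute points, leaves its primary measure open between an adjusted risk ratio and an adjusted odds ratio, and names no absolute difference. The same planned effect would be reported as about 1.4 or about 2.3, and neither figure identifies a 20-point effect unless the control rate is as assumed. This rests on the article's own control rates; the other control rates in step 3 are illustrative. It does not threaten the validity of the comparison and costs almost no power. The self-efficacy part is a free gain in precision whose size depends on a correlation that the documents do not give.

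**What to change.** Before outcome data are seen, state one primary measure for EBF and AACF at 6 months: the adjusted risk difference with 95% CI, obtained by marginal standardisation of the logistic model (in Stata, margins after the fit, with robust standard errors). Report the risk ratio from the same model beside it, and do not use the odds ratio as the headline for the primaries. If multiple imputation is triggered, compute the standardised estimates in each imputed data set and combine them. The covariate list can stay in the analysis plan, provided that it too is fixed in advance.

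For breastfeeding self-efficacy at 14 weeks and 12 months, state that the recruitment score is included as a covariate.

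The cost is a few sentences. No new data and no change in sample size are needed. Timing allows it at the article's dates: recruitment began on 2 February 2026, so even a birth on that day would not reach the 6-month visit, with its 2-week window, before mid-July 2026, and the article reports recruitment only to 18 May 2026.
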